## PROJECT PROPOSAL

Name of the Project: **Transcranial direct current stimulation (tDCS) as a therapeutic intervention for post-acute sequelae of SARS-CoV-2 (PASC)**

Název projektu: **Transkraniální stimulace stejnosměrným proudem (tDCS) jako léčebná intervence pro zotavení z post-akutních následků SARS-CoV-2 (PASC)**

**NUDZ Principal Investigator:** [name]., Ph.D.

**Aim of the study:** The main aim of this project is to evaluate the clinical efficacy and safety of transcranial direct current stimulation (tDCS) of the dorsolateral prefrontal cortex (DLPFC) in the treatment of neuropsychiatric symptoms of the post-acute sequelae of SARS-CoV-2 infection (PASC). The primary objective of the double-blind, randomized, placebo-controlled, parallel study with four-week follow-up is to compare the efficacy (response to the treatment, effect duration) and safety of 4-week active DLPFC-tDCS (20 tDCS applications with anode placement at F3; 2 mA, 30 min/tDCS session) to placebo-tDCS in the treatment of neuropsychiatric symptoms of PASC. The primary study outcome is a change in validated Czech version of the "Fatigue Impact Scale" (FIS) after the acute phase of the study and after the follow-up. Secondary outcomes will cover 1) the change in the following measurements: a) functional ability, cognitive functions, and emotional symptoms subscales of the "Post-COVID-19 Symptoms Assessment Questionnaire" (A-PASC), b) self-assessment scales of depressive and anxiety symptoms (PHQ-9; GAD-7), c) cognitive testing focused on attention, working memory, and psychomotor pace, d) quality of life monitoring based on the AQOL-6D questionnaire after the acute phase of the study and after the follow-up, and 2) evaluation of tDCS side effects during tDCS treatment. The secondary outcomes will target the electrophysiological (EEG) parameters associated with PASC and their changes after the intervention with respect to the assigned group and response rate (specifically qEEG cordance, EEG microstates, and functional connectivity will be evaluated).

**Duration of the study:** 04/2022 – 12/2023

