### Methodology:

**Study design:** Randomized control trial with active (n=17) and sham (n=17) group.

**Subjects:** 34 patients will be included in the study. Patients will be on stable medication for at least four weeks at the time of study entry. Patients will be recruited from inpatients and outpatients of Národní ústav duševního zdraví (NUDZ).

**Inclusion criteria:** 1. Male and female outpatients aged 18-75 years with a history of COVID-19 and monitored by an outpatient physician for mental disorders (anxiety, mood disorders, sleep) within the PASC; 2. PCR RNA SARS-CoV-2 negativity at screening/study entry; 3. Duration of symptoms >1 and ≤24 months after detection of COVID-19; 4. The mental ability to understand and sign the Informed Consent Form; 5. Presence of neuropsychiatric PASC symptoms as determined by A-PASC with a minimum overall score ≥25 (cognitive score, emotional and functional impairment); 6. FIS questionnaire score ≥40; 7. Psychopharmacological medication (if used) at a stable dose ≥4 weeks.

**Exclusion criteria:** 1. Contraindications of tDCS (skin disease, superficial injury, and fracture or infraction of skull in the stimulation area, epilepsy, metallic plates in the head); 2. History of any other DSM-IV axis I diagnosis prior to COVID-19, except for: 2.1. Depressive disorders, anxiety disorders, and sleep disorders that may be present in the history, but with at least 6 months of documented remission of symptoms, 2.2. Disorders associated with the use of addictive substances at least 6 months before entering the study; 3. Pregnancy or breastfeeding; 4. Patients with severe and/or unstable somatic disorders (cardiovascular disease, neoplasms, endocrinology disorders, etc); 5. Patients suffering from a serious neurological disorder (eg epilepsy, head injury with loss of consciousness)

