**Treatment trial:**

Patients included in the study will be examined by FIS, A-PASC, AQoL, PHQ, GAD-7, and Clinical Global Impression (CGI) questionnaires to determine neuropsychiatric symptoms and the current symptom severity at study entry, at initiation, during (after 2 weeks), at the end of 4 weeks of tDCS treatment and with an interval of 4 weeks after. Attention-oriented cognitive tests (computer variant) (Digit Span - forward span), working memory (Digit Span - backwards span) and psychomotor tempo (Digit Symbol Substitution Test) will be performed at the beginning and subsequent follow-ups. In addition, three EEG examinations will be performed during the study (before the start of tDCS, after two weeks of tDCS, and at the end of tDCS treatment).

Patients will be randomly allocated according to permuted block design to one of two intervention groups: active anodal tDCS or placebo anodal tDCS.

Each tDCS session (active or placebo) will last 30 minutes. A total of 20 tDCS sessions will be administered to patients over four weeks.

The HDCStim programmable stimulator (Newronika, Italy) available for a double-blind design will be used for the application of tDCS.

**Statistical analysis plan:** Efficacy and safety data will be obtained from the modified intention-to-treat (mITT) dataset, consisting of patients randomized to treatment and receiving at least one tDCS session. To estimate changes in the primary outcome measurement, the Fatigue Impact Scale (FIS) total score, from baseline to week four and follow-up, a mixed model for repeated measures (MMRM) with a restricted maximum likelihood (REML) approach and Kenward-Roger adjustment of degrees of freedom will be employed. Least-squares (LS) means, within and between-group differences in LS means, and corresponding 95%CI will be calculated, and Sidak correction will be applied. Secondary outcomes (FIS subscales, A-PASC total score and subscales, PHQ-9, GAD-7, cognitive tests, and AQOL-6D) will be subjected to the same MMRM analysis, with covariate selection adapted to each outcome. The occurrence of side effects will be compared by Fisher's exact test.

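### EEG change should be related to continuous FIS change, not to a response rate: a responder split loses at least about 36% of the information in 34 patients

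*Protocol*

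**What the plan says.** In the Aim of the study, the Protocol makes EEG parameters (cordance, microstates, functional connectivity) a secondary outcome, to be studied together with "their changes after the intervention with respect to the assigned group and response rate". It gives no scale, cut-off or time point for response.

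FIS is treated as continuous throughout. The Statistical analysis plan paragraph under Treatment trial fits an MMRM "To estimate changes in the primary outcome measurement, the Fatigue Impact Scale (FIS) total score, from baseline to week four and follow-up". The other listed outcomes follow the same route: "Secondary outcomes (FIS subscales, A-PASC total score and subscales, PHQ-9, GAD-7, cognitive tests, and AQOL-6D) will be subjected to the same MMRM analysis". Neither EEG nor responder status is in that list.

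On timing, the Treatment trial section says that "three EEG examinations will be performed during the study (before the start of tDCS, after two weeks of tDCS, and at the end of tDCS". FIS is also measured at the start, after two weeks and at the end of treatment. On size, the Methodology section says "34 patients will be included in the study", 17 per arm.

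**The concern.** A response rate is a proportion in a group. To relate it to the EEG change of individual patients, each patient needs a label, and the natural one is responder or non-responder. That would turn a graded FIS change into two categories, so that a patient just past the cut-off counts the same as one who improved greatly, and a near miss counts the same as no change.

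In a large trial this cost might be tolerable. With 34 patients at most, the EEG-by-response question has little information to spare. A real association between EEG change and improvement in fatigue could easily be missed, and a null result would say little. The loss comes from the method and is avoidable, because the continuous FIS change is collected anyway.

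**Working it through.** The Protocol states no alpha, power, effect size, SD, responder share or EEG–FIS correlation, so it has no figure of its own to reproduce. The results below are conditional.

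**Inputs**
- n = 34, 17 per arm (Methodology), all assumed to complete.
- Assumed: EEG change and FIS change approximately bivariate normal; responder share p from 50% down to 20%; two-sided alpha 0.05; true correlation r of 0.3 to 0.5.

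**Step 1. Information kept by a split.** When a normal variable is cut so that a share p lies on one side, the information kept relative to the continuous form is φ(z_p)² / [p(1 − p)], where φ is the standard normal density.
- p = 0.5: 0.3989² / 0.25 = 0.637. Loss 36.3%, equivalent to 34 × 0.637 = 21.6 patients.
- p = 0.3: 0.3477² / 0.21 = 0.576. Loss 42.4%, equivalent to 19.6 patients.
- p = 0.2: 0.2800² / 0.16 = 0.490. Loss 51.0%, equivalent to 16.7 patients.

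The expression is largest at p = 0.5. So 36% is the smallest loss that any two-way split of a normal variable can have, whereas 51% holds only for a 20% responder share.

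**Step 2. Power for the EEG–FIS association.** By Fisher's z, power ≈ Φ(atanh(r) × √(34 − 3) − 1.96). After a split, r is multiplied by the square root of the information kept: 0.798 at 50/50, 0.759 at 30/70 and 0.700 at 20/80.

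Worked case, r = 0.5:
- Continuous: atanh(0.5) = 0.549; 0.549 × 5.568 = 3.058; Φ(3.058 − 1.96) = 86.4%.
- 50/50 split: 0.5 × 0.798 = 0.399; atanh = 0.422; 0.422 × 5.568 = 2.352; Φ(0.392) = 65.2%.

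| True r | Continuous | 50/50 | 30/70 | 20/80 |
|---|---|---|---|---|
| 0.3 | 40.6% | 27.4% | 25.1% | 22.0% |
| 0.4 | 65.5% | 45.3% | 41.5% | 36.0% |
| 0.5 | 86.4% | 65.2% | 60.4% | 53.0% |

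**Step 3. Check by simulation** (20,000 runs, n = 34). In the same column order, r = 0.5 gave 87.4%, 66.9%, 61.2% and 53.8%; r = 0.4 gave 66.3%, 46.1%, 41.1% and 35.5%. The approximation is adequate.

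**Step 4. Can the continuous analysis be done?** Yes. EEG and FIS are both measured before treatment and at its end, so each patient with both visits contributes a pair of changes. Adding assigned group as a covariate costs about one degree of freedom. With √30 in place of √31 and r read as a partial correlation, the r = 0.5 continuous figure becomes Φ(0.549 × 5.477 − 1.96) = Φ(1.05), about 85%.

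**The case against.** The strongest reply is that this is a short proposal, that the meaning of response and the EEG model are details commonly left to a statistical analysis plan, and that a separate plan may exist. The term could also be loose wording for degree of response, which would already be the analysis recommended here, or it could rest on the CGI, which is collected.

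Part of this stands. That response is undefined in this document is not in itself a fault, and the point does not rest on it. What remains is the choice that the wording makes. Read plainly, response rate calls for a responder label, and a label fixed in advance on FIS loses the same information as one fixed late. A label based on CGI would leave the graded FIS data unused for this question. If continuous change was meant, the wording should say so.

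Three stronger readings are tempting, and the document does not support them.
- A reader might infer that the cut-off must be chosen after the data are seen, with an inflated false-positive rate. No passage says so, and an unseen plan may fix it. Any inflation figure would rest on invented cut-offs and on selective picking that nothing in the text suggests.
- A reader might infer that the primary objective, which says it will "compare the efficacy (response to the treatment, effect duration) and safety", needs a responder endpoint too. The next sentence gives that phrase its meaning: FIS change after the acute phase and after follow-up. The MMRM estimates both.
- A reader might infer, from the reference to EEG parameters linked with PASC, a comparison that needs people without PASC. None is stated; the phrase describes which parameters are of interest.

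**Conclusion.** The point holds for one secondary question. Relating EEG change to a responder label, in place of continuous FIS change, costs at least about 36% of the information in 34 patients if FIS change is approximately normal, and about 51% if only 20% respond. For an assumed correlation of 0.5, power falls from about 86% to 65% at an even split and to 53% at 20/80. The lower bound on the loss depends only on normality. The 51% and all the power figures depend on assumed responder shares and correlations. Dropout would lower power under either method.

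The comparison of EEG change by assigned group needs no split and loses nothing. Nor does the primary FIS comparison. The change is worth making because it is cheap, but the trial's main conclusion does not depend on it.

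**What to change.** In the Aim of the study, replace response rate in the EEG sentence with each patient's change in FIS total score from baseline to week 4, as a continuous variable. Relate EEG change over the same interval to it, with assigned group in the model. Report the association with a 95% confidence interval.

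If a responder comparison is still wanted, label it supportive and fix its scale, cut-off and time point in writing before unblinding.

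The cost is one reworded phrase and one specified EEG model. No extra visits, measurements or patients are needed. The downside is that no responder versus non-responder comparison is headlined, which some readers find easier to grasp; the supportive analysis can meet that need.

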### Methodology:

**Study design:** Randomized control trial with active (n=17) and sham (n=17) group.

**Subjects:** 34 patients will be included in the study. Patients will be on stable medication for at least four weeks at the time of study entry. Patients will be recruited from inpatients and outpatients of Národní ústav duševního zdraví (NUDZ).

**Inclusion criteria:** 1. Male and female outpatients aged 18-75 years with a history of COVID-19 and monitored by an outpatient physician for mental disorders (anxiety, mood disorders, sleep) within the PASC; 2. PCR RNA SARS-CoV-2 negativity at screening/study entry; 3. Duration of symptoms >1 and ≤24 months after detection of COVID-19; 4. The mental ability to understand and sign the Informed Consent Form; 5. Presence of neuropsychiatric PASC symptoms as determined by A-PASC with a minimum overall score ≥25 (cognitive score, emotional and functional impairment); 6. FIS questionnaire score ≥40; 7. Psychopharmacological medication (if used) at a stable dose ≥4 weeks.

**Exclusion criteria:** 1. Contraindications of tDCS (skin disease, superficial injury, and fracture or infraction of skull in the stimulation area, epilepsy, metallic plates in the head); 2. History of any other DSM-IV axis I diagnosis prior to COVID-19, except for: 2.1. Depressive disorders, anxiety disorders, and sleep disorders that may be present in the history, but with at least 6 months of documented remission of symptoms, 2.2. Disorders associated with the use of addictive substances at least 6 months before entering the study; 3. Pregnancy or breastfeeding; 4. Patients with severe and/or unstable somatic disorders (cardiovascular disease, neoplasms, endocrinology disorders, etc); 5. Patients suffering from a serious neurological disorder (eg epilepsy, head injury with loss of consciousness)

**Treatment trial:**

Patients included in the study will be examined by FIS, A-PASC, AQoL, PHQ, GAD-7, and Clinical Global Impression (CGI) questionnaires to determine neuropsychiatric symptoms and the current symptom severity at study entry, at initiation, during (after 2 weeks), at the end of 4 weeks of tDCS treatment and with an interval of 4 weeks after. Attention-oriented cognitive tests (computer variant) (Digit Span - forward span), working memory (Digit Span - backwards span) and psychomotor tempo (Digit Symbol Substitution Test) will be performed at the beginning and subsequent follow-ups. In addition, three EEG examinations will be performed during the study (before the start of tDCS, after two weeks of tDCS, and at the end of tDCS treatment).

Patients will be randomly allocated according to permuted block design to one of two intervention groups: active anodal tDCS or placebo anodal tDCS.

Each tDCS session (active or placebo) will last 30 minutes. A total of 20 tDCS sessions will be administered to patients over four weeks.

The HDCStim programmable stimulator (Newronika, Italy) available for a double-blind design will be used for the application of tDCS.

**Statistical analysis plan:** Efficacy and safety data will be obtained from the modified intention-to-treat (mITT) dataset, consisting of patients randomized to treatment and receiving at least one tDCS session. To estimate changes in the primary outcome measurement, the Fatigue Impact Scale (FIS) total score, from baseline to week four and follow-up, a mixed model for repeated measures (MMRM) with a restricted maximum likelihood (REML) approach and Kenward-Roger adjustment of degrees of freedom will be employed. Least-squares (LS) means, within and between-group differences in LS means, and corresponding 95%CI will be calculated, and Sidak correction will be applied. Secondary outcomes (FIS subscales, A-PASC total score and subscales, PHQ-9, GAD-7, cognitive tests, and AQOL-6D) will be subjected to the same MMRM analysis, with covariate selection adapted to each outcome. The occurrence of side effects will be compared by Fisher's exact test.

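### Safety is in the primary objective, but side effects are evaluated only during treatment and the only comparison named is a test with low power for moderate excesses at 17 per arm

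*Protocol*

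**What the plan says.** The Aim of the study paragraph describes a "parallel study with four-week follow-up" whose primary objective "is to compare the efficacy (response to the treatment, effect duration) and safety of 4-week active DLPFC-tDCS" against placebo stimulation. Safety therefore stands beside efficacy in the objective. The same paragraph names the FIS change as the primary outcome and lists safety among the secondary outcomes, as "evaluation of tDCS side effects during tDCS treatment". The FIS and the clinical, cognitive and quality-of-life measures are to be assessed both after the acute phase and after the follow-up. The side-effect outcome is the one with a treatment-only window.

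The Treatment trial section schedules a questionnaire assessment four weeks after the end of stimulation. Its Statistical analysis plan paragraph takes safety data from the mITT set (randomised, at least one session). For the mixed-model outcomes it commits to between-group differences and says the "corresponding 95%CI will be calculated". For side effects the single sentence begins "The occurrence of side effects will be compared by Fisher", that is, Fisher's exact test. It states no significance level, sidedness, expected rate or interval for them.

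The Methodology section gives the size: "Randomized control trial with active (n=17) and sham (n=17) group".

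**The concern.** Two features limit what the trial can say about half of its stated objective.

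The first is the window. Duration of benefit is followed for four weeks after the last session, but the safety outcome ends with the last session. A side effect that appears or persists afterwards would fall outside the defined outcome, although patients are assessed again at the end of follow-up.

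The second is the form of the result. For efficacy the protocol promises an estimate with an interval; for side effects it names only a significance test. With 17 per arm, a moderate excess on active stimulation will usually give a non-significant p-value. That p-value does not tell the reader whether the data exclude a 30- or 40-point excess.

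**Working it through.** **Inputs.** Arms of 17 and 17 (Methodology). Fisher's exact test (Statistical analysis plan paragraph). The level is not stated for side effects; two-sided 5% is assumed, in line with the 95% intervals used for the other outcomes. Side-effect rates are not given, so a range is shown. The protocol states no power or size for this comparison, so there is no figure of its own to reproduce.

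**Smallest significant tables.** With all events in one arm, the two-sided Fisher p is 2 × C(17,k)/C(34,k).
- 4/17 v 0/17: 2 × 2380/46376 = 0.103.
- 5/17 v 0/17: 2 × 6188/278256 = 0.044.

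So 5 v 0 is the first significant result against zero. Against one sham event, seven active events are needed; 5/17 v 1/17 gives p = 0.175.

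**Power.** Sum over all 18 × 18 tables of Bin(i; 17, p_active) × Bin(j; 17, p_sham), keeping tables with Fisher p ≤ 0.05.

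| Active v sham rate | Power |
|---|---|
| 20% v 0% | 24% |
| 30% v 10% | 19% |
| 40% v 20% | 14% |
| 50% v 30% | 14% |
| 50% v 20% | 32% |
| 50% v 10% | 63% |
| 30% v 0% | 61% |
| 40% v 0% | 87% |
| 70% v 20% | 79% |

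Power of 80% needs an active rate of about 37% against 0% on sham, 59% against 10%, or 71% against 20%.

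**No events.** The exact (Clopper-Pearson) upper 95% limit for 0/17 is 1 − 0.025^(1/17) = 0.195, or 19.5%.

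**What an interval adds.** The Newcombe interval for a risk difference combines the Wilson limits of the two arms.
- 4/17 v 0/17: difference 0.235. Wilson limits are 0.096 to 0.473 (active) and 0 to 0.184 (sham). Lower: 0.235 − √[(0.235 − 0.096)² + 0.184²] ≈ 0.004. Upper: 0.235 + (0.473 − 0.235) ≈ 0.473. About +0.4 to +47 points.
- 5/17 v 1/17: difference 0.294 − 0.059 = 0.235. Wilson limits are 0.133 to 0.531 and 0.010 to 0.270. Lower: 0.235 − √[(0.294 − 0.133)² + (0.270 − 0.059)²] ≈ −0.03. Upper: 0.235 + √[(0.531 − 0.294)² + (0.059 − 0.010)²] ≈ 0.48. About −3 to +48 points.

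Both tables are non-significant by Fisher's test, and both are compatible with an excess of more than 40 points. In the first, the Newcombe interval just excludes zero while Fisher's p is 0.10. The two methods can disagree at the margin, so the plan should say which one leads.

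**Boschloo's test as an alternative.** Its maximum size at 17 v 17 is 4.3%, so it holds 5%. Power rises from 32% to 43% for 50% v 20%, and from 19% to 21% for 30% v 10%. It is unchanged for 30% or 40% v 0%. It does not reject 4 v 0 (p = 0.058) or 5 v 1 (p = 0.12).

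**The case against.** Fisher's test is a standard, valid choice for small 2 × 2 tables. Its true size is below 5% (maximum 2.4% at exactly 17 v 17), but that is a known property of an exact test, not an error. The figure is also fragile: the mITT rule can leave unequal arms, and at 16 v 17 the maximum is 3.5%. What limits information is mainly the 17 per arm. All of this stands, so the point does not rest on the size of the test, and a change of test is optional.

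A reader might infer that a finding of no difference is all but guaranteed. The numbers do not support that: power is 61% for 30% v 0%, 63% for 50% v 10% and 87% for 40% v 0%. A reader might also infer that the investigators will read non-significance as proof of safety. The protocol says only that occurrence will be compared.

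An on-treatment window is a defensible choice for a stimulation procedure, and a secondary safety outcome under a broader objective is common. Nor does the protocol say that later events would go unreported. This makes the point milder, but the protocol gives no reason for ending the safety outcome at the last session while its objective attaches the follow-up to efficacy and safety alike.

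Finally, risk differences and intervals may be in a statistical analysis plan that is not shown. That is possible, and their absence alone would not be a finding. What remains is that the protocol's own analysis paragraph fixes an estimate with an interval for efficacy and only a test for side effects.

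**Conclusion.** The point holds in a limited form. The safety outcome covers a shorter period than the objective implies, and the one comparison named for it has about 14% to 32% power for the moderate excesses of 20 to 30 points examined where side effects also occur on sham (10% to 30%). It has 61% to 87% power for 30% to 40% against none. With no events at all, a true rate of up to 19.5% in an arm is not excluded. These figures assume 17 analysed per arm, a two-sided 5% level and illustrative rates, none of which the protocol states for side effects; unequal arms would shift them. This does not invalidate the trial or the test. It means that a p-value alone would answer the safety part of the objective poorly, and that two inexpensive changes would answer it better.

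**What to change.** 1. Record side effects at the assessment already scheduled four weeks after treatment, and tabulate the treatment and follow-up periods separately. Amend the outcome definition in the Aim of the study paragraph to match.
2. For each side effect, count patients with at least one occurrence. Make the active-minus-sham risk difference with a 95% CI (for example Newcombe's) the main safety result.
3. Keep Fisher's test as supportive, and state its level and sidedness. Boschloo's test may replace it: it holds 5% and is never less powerful, but the gain is small or nil in several settings.

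The cost is one checklist at an existing visit and minor extra analysis. No added visit is needed.
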